### Clinical and laboratory evaluations

A physical examination, laboratory evaluations, and medication reviews will be conducted before treatment. The laboratory evaluations including the arterial blood gas analysis (ABGA) will be performed based on the usual clinical practice, and additional examinations will be conducted if it is deemed necessary for treatment (irrespective of the study).

### Safety issues

The participants will be monitored for blood pressure, heart rate, respiratory rate, saturations, and electrocardiogram (ECG) during the study period. We will check for any clinical signs of deterioration and for patients’ discomfort at every time point. All adverse events related to the study will be recorded and followed up during the study period. Any serious adverse events will be reported to investigators and the ethics committee.

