To the best of our knowledge, there is only one study into weaning protocols for the HFNC, which was conducted within a pediatric intensive care unit (ICU) [17]. The authors suggested a “holiday” weaning protocol. In the holiday protocol, patients scoring less than or equal to 6 qualified for a HFNC holiday trial on low-flow nasal cannula settings. Patients with a respirator assessment score (RAS) of 7 or 8 had HFNC flow decreased by half, and patients scoring more than 8 remained on current settings and were reassessed. If their RAS remained less than 6, a holiday patient stayed on a low-flow nasal cannula and continued traditional weaning based on oxygen saturations. If the RAS was 6–8, the patient was put on half the amount of flow and scoring was repeated. If the repeat RAS was greater than 8, holiday patients returned to initial settings. Out of 133 patients, 119 (89.5%) successfully weaned to low-flow nasal cannula within four holiday attempts, and 14 (10.5%) failed to be weaned. Though the holiday weaning method seems efficient, we have some concerns relating to its clinical application. First, this study was not designed for comparison of different methods of HFNC withdrawal. Second, there is a lack of detailed information about HFNC application and the risk of atelectotrauma. Last, this study included only children. This makes it hard to extrapolate to adults with HFNC. We are conducting this randomized controlled trial (RCT) to investigate the safety and efficacy of simultaneous reduction of the two variables compared to sequentially reducing either the flow first, or the fraction of inspired oxygen (FiO_2_) first for the withdrawal of the HFNC in adult patients who are stable and ready to be weaned.

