### Randomization

A research coordinator will randomize the participants. An independent statistician will generate a list of random numbers. Eligible participants will be randomly assigned at a ratio of 1:1:1 to the flow reduction first (FR) group, the FiO_2_ reduction first (OR) group, or the simultaneous reduction (SR) group, in accordance with the predefined randomization list with a block size of 3. Information about the randomization will not be provided to the research supervisor, co-researcher, or patients. In the case of an emergency, co-researchers who are aware of the random assignments should avoid participating in future results analysis.

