### Types of interventions

After randomization, the participants will undergo FR, OR, or SR strategies for weaning off the HFNC. In the FR group, flow will gradually be reduced by 10 L/min/h. When it reaches 20 L/min, FiO_2_ reduction will then begin at 0.1 /h until it reaches 0.3. In the OR group, FiO_2_ will gradually be reduced by 0.1 /h until it reaches 0.3. At this point, flow will be reduced by 10 L/min/h until it reaches 20 L/min. Finally, in the SR group, both flow and FiO_2_ will be gradually reduced simultaneously at a rate of 10 L/min and 0.1 /h, respectively, until they reach the HFNC weaning-off targets (20 L/min for flow and 0.3 for FiO_2_). Weaning will proceed only when the patient satisfies all the weaning criteria at every weaning point. When flow and FiO_2_ reach weaning-off targets, the patient will be transferred to conventional oxygen therapy, such as low-flow nasal prongs.

We have followed the Standard Protocol Items: Recommendations for Interventional Trials (SPIRIT) 2013 statement, which defines the standard protocol items for clinical trials [18] (see Additional file 1). The study algorithm is depicted in Fig. 1 and the SPIRIT schedule is shown in Fig. 2.

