### Data and safety monitoring

The paper data collection sheets and signed informed consents will be stored in a locked cabinet, and the electronic database will be stored on password-protected secure severs. Any unanticipated adverse events that occur during the study will be reported to the Institutional.

Review Board in accordance with the procedures of Seoul National University Bundang Hospital, Korea. Any proposed revised study procedure will be submitted to the Seoul National University Bundang Hospital Institutional Review Board for approval and to

ClinicalTrials.gov. The data will be kept confidential with only limited access to research investigators.

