## Discussion

The HFNC is usually applied in critically ill patients. We therefore considered a study design that would minimize the risk to the patients. First, we adopted strict criteria for both patient inclusion and the weaning process to ensure patient safety. Second, we decided to compare three stepwise weaning protocols for HFNC without including immediate withdrawal from HFNC. The potential advantage of immediate withdrawal is a considerable shortening of the weaning process. However, risk of failure and the need for reinstitution of the HFNC or intubation is a major concern. In contrast to immediate withdrawal, stepwise weaning may minimize atelectotrauma and gradually increase respiratory muscle strength without the associated risk of atelectasis. Finally, the attending physician and nurse are requested to assess the patient’s condition within 30 min of changing the HFNC setting. In this study, several clinical outcomes will be compared between these three groups. After completion of the study, we hope to be able to suggest the best strategy for the withdrawal of the HFNC in adult patients.

There are several strengths of this study design. This will be the first study to evaluate HFNC weaning strategies in an adult population. It has been designed as a prospective RCT, which is one of the most powerful study designs. Furthermore, we will not conduct any medical tests or interventions other than HFNC weaning in this study in order to reflect the actual clinical situation. There are also some limitations of this study, namely, the small sample size and the fact that the study will be conducted at a tertiary referral hospital. In addition, we will adopt 1-h interval weaning, which is slower than the HFNC weaning process used in clinical practice. However, it was a necessary choice to ensure patient safety. Given the shortcomings of this first study, further additional studies will eventually be required on larger scale.

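### Non-serious, anticipated adverse events are recorded only if considered related to the study, in a trial where bedside staff can see the arm

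*Protocol article*

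**What the plan says.** The recording rule is in the protocol article under Safety issues: "All adverse events related to the study will be recorded and followed up during the study period". The sentence after it has no relatedness condition: "Any serious adverse events will be reported to investigators and the ethics committee". Data and safety monitoring adds a second unconditional rule: "Any unanticipated adverse events that occur during the study will be reported to the Institutional" Review Board. Safety issues also lists continuous or repeated monitoring of vital signs and ECG, and states "We will check for any clinical signs of deterioration and for patients", the sentence going on to discomfort at every time point.

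Safety is part of the stated aim. Background says that the trial is to "investigate the safety and efficacy of simultaneous reduction of the two variables" against the two sequential strategies.

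On masking, Randomization says "Information about the randomization will not be provided to the research supervisor, co-researcher, or patients". Bedside physicians and nurses are not in that list. The intervention consists of visible device settings: in the SR arm "both flow and FiO_2_ will be gradually reduced simultaneously", and in the other two arms one setting is taken down before the other (Types of interventions). The Discussion adds that "the attending physician and nurse are requested to assess" the patient within 30 min of each change of setting.

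**The concern.** Relatedness is usually recorded about an event after the event has been logged. Here it decides whether the event is logged at all. An event judged unrelated leaves no adverse event record, and no later analysis can recover it.

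This matters more here than in many trials. The patients are often critically ill, so a short desaturation or a run of tachycardia can be put down either to the underlying disease or to the weaning step. Someone who can see that both settings have just been lowered may be readier to blame weaning than someone who saw only one lowered, or may lean the other way. If attribution differs by arm, the recorded counts mix true differences with differences of opinion. What is at stake is the description of minor and moderate harms in a trial that says it will assess safety.

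**Working it through.** The plan states no figure on this point, so there is nothing to reproduce. The check has two parts: which events can be lost, and how far assumed differences in attribution could move recorded counts.

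**Which events can be lost**

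| Type of event or outcome | Depends on relatedness? | Where |
|---|---|---|
| Serious adverse event | No | Safety issues |
| Unanticipated adverse event | No | Data and safety monitoring |
| Weaning failure (HFNC re-applied, NIV, intubation) | No | Definitions |
| Intolerance, blood gas changes, in-hospital mortality | No | Outcome measures |
| Non-serious, anticipated adverse event | Yes | Safety issues |

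Only the last row is exposed. Within it, some events still leave a trace elsewhere. Weaning moves on only if every weaning criterion is met at each step, and the criteria include saturation, respiratory rate, heart rate, systolic pressure and absence of distress. A breach present at a weaning point therefore delays the wean and lengthens the primary outcome, and a breach present at 24 h after conversion prevents success. An episode that starts and resolves between checks, or an arrhythmia with the heart rate inside the limit, does neither. Blood gases follow usual practice (Clinical and laboratory evaluations), so they need not catch such an episode.

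**Illustration with assumed rates**

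Inputs: 100 participants over three arms, so about 33 per arm (Sample size calculation). The true risk r of a non-serious event, taken as equal in two arms, and the proportions q1 and q2 judged related are assumptions; the documents give none of them.

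Recorded rate = r × q. Spurious difference = r × (q2 − q1).

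- r = 30%, q = 50% v 70%: 0.30 × 0.50 = 15% v 0.30 × 0.70 = 21%, a difference of 6 points. In 33 patients per arm, about 10 have an event (0.30 × 33 = 9.9), of which about 5 v 7 are recorded.
- r = 30%, q = 40% v 80%: 12% v 24%, a difference of 12 points, or about 4 v 8 recorded.
- r from 20% to 40%: 4 to 8 points for 50% v 70%, and 8 to 16 points for 40% v 80%.
- q1 = q2: no spurious difference.

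A true difference can also be hidden: 20% v 10% with 25% v 50% judged related gives 0.20 × 0.25 = 5% and 0.10 × 0.50 = 5%.

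The chance that the artefact reaches two-sided p < 0.05 at n = 33 per arm, by normal approximation, is Φ[(|p2 − p1| − 1.96 × SE0)/SE1], where SE0 = √(2p̄(1 − p̄)/n) and SE1 = √((p1(1 − p1) + p2(1 − p2))/n). For 12% v 24%, SE0 = √(2 × 0.18 × 0.82/33) = 0.0946 and SE1 = √((0.1056 + 0.1824)/33) = 0.0934, so the result is Φ[(0.12 − 0.1854)/0.0934] = Φ(−0.70) = 0.24. Over the six unequal scenarios (r = 20%, 30%, 40%) it runs from about 7% to about 33%.

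**The case against.** The strongest reply is that the outcomes that carry the safety question are untouched. The Hypothesis section frames safety as shorter weaning with no rise in weaning failure, and failure is defined by what was done to the patient, with no attribution. Intolerance, blood gases and mortality likewise need none. No comparison of adverse event counts between arms is listed under Outcome measures. All of this stands, and it limits the point to a secondary description of harms.

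Two stronger readings are tempting. A reader might infer that related events are the only ones captured, so that the whole safety comparison is filtered. The documents do not support that: serious and unanticipated events are reported regardless of cause, and the listed outcomes do not depend on relatedness. A reader might also infer that the judgement is made by unmasked staff. That is not stated either. The supervisor and co-researcher are not given the allocation, so a masked assessor is possible. Who judges relatedness, and by what criteria, is commonly left to the full protocol; its absence from an article is not a fault.

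It may also be said that deterioration and discomfort are checked at every time point. They are, but a check is not a record, and the sentence that follows confines adverse event recording to related events. That recording rule is stated outright, so it is open to comment even though the full protocol is not shown.

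**Conclusion.** The point holds in a limited form. As written, the rule allows non-serious, anticipated events to go unrecorded as adverse events after a relatedness judgement by an unnamed assessor, while bedside staff can tell the arm from the settings. The safety evaluation is affected in part, not as a whole.

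Neither the size nor the direction of any bias can be derived from the documents. The spurious differences of 4 to 16 points rest wholly on assumed risks of 20% to 40% and assumed gaps in attribution, and they vanish if attribution is equal across arms. Even under those assumptions the artefact would usually not reach p < 0.05. The likelier harm is an incomplete and possibly uneven count of minor events. The primary analysis, the listed secondary outcomes and serious-event reporting do not depend on this rule. It is worth changing because the change is cheap and lost events cannot be recovered.

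**What to change.** Reword the sentence under Safety issues so that all adverse events, whatever their cause, are recorded in every arm from randomisation to 24 h after conversion to conventional oxygen therapy. Make relatedness a separate field completed after the event is logged, by an assessor masked to arm where that is feasible. Summarise all events by arm, with the related subset shown beside them. Leave the unconditional reporting of serious and unanticipated events as it is.

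The cost is one changed sentence, one field on the case report form, and somewhat more logging in sick patients. The window is short and the patients are already monitored throughout it, so no new observations are needed.

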### Sample size calculation

It is difficult to calculate the target number of patients, because this is the first RCT evaluating the best strategy for weaning off the HFNC. Considering that 30 patients were compared in the NIV weaning protocol study, we estimate that a total of 90 participants, 30 in each group, would be needed. A total of 100 participants will be recruited in anticipation of a 10% dropout rate in each group based on the recent HFNC weaning study [17]. We have prepared for one interim analysis at the time when half of the subjects have completed the study.

### Statistical analyses

Statistical analyses will be performed on both a per-protocol (PP) and an intention-to treat (ITT) basis. For the PP analysis, all participants who complete the study will be included to evaluate the primary and secondary outcomes. For the ITT analysis, all participants enrolled and randomized to one of the three groups will be included. In the interim analysis, if the *P* value is < 0.003, we will stop the study early, accepting the significance of the outcome. If not, we will recruit the remaining half of the subjects. Sub-group analysis according to the respiratory failure type (hypoxemic or hypercapnic) is planned. Unless otherwise specified, continuous variables will be expressed as mean plus standard deviations or median and categorical variables as percentages. Student’s *t* test will be used to compare continuous variables; the chi-square or Fisher’s exact test will be used to compare categorical variables. Unless otherwise stated, all tests are two-sided and performed at the 0.05 significance level. Analyses will be performed using SPSS 20.0 (IBM Corp., Armonk, NY, USA).

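### The interim stopping rule names no comparison or analysis set and no condition on weaning failure, and the final test stays at 0.05 after a 0.003 look (a small excess)

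*Protocol article*

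**What the plan says.** Under Sample size calculation the article states: "We have prepared for one interim analysis at the time when half of the subjects have completed the study". Statistical analyses then gives the rule. When the interim P falls below 0.003, the text reads "we will stop the study early, accepting the significance of the outcome". Otherwise the trial goes on: "If not, we will recruit the remaining half of the subjects".

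The same section sets a default for every analysis: "all tests are two-sided and performed at the 0.05 significance level". That default yields only where another level is stated, and none is stated for the final analysis.

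The rule has to operate within the following design:

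- Randomization sets three arms: "Eligible participants will be randomly assigned at a ratio of 1:1:1".
- Statistical analyses compares continuous variables by Student's t test, a two-group test. It analyses both the ITT and the PP set and calls neither primary.
- Outcome measures names one primary outcome, time to successful weaning.
- Hypothesis has two parts: a shorter weaning time with simultaneous reduction (SR) than with flow first (FR) or FiO2 first (OR), and no increase in weaning failure.

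**The concern.** There are three separate gaps, and they differ in weight.

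1. **Which P value.** An efficacy stop cannot be undone, so its trigger should be a single test fixed in advance. Here the primary outcome alone offers three pairs in two analysis sets, that is 3 × 2 = 6 candidate P values. One SR comparison could stop the trial while the other is unresolved. Even FR against OR, which is not part of the hypothesis, would satisfy the wording.
2. **No look at failure.** The hypothesis is about speed without more failures. The rule can declare success on speed alone, when the information on failure is at its thinnest.
3. **Final level.** Some type I error is spent at the interim, yet the final test keeps the full 0.05. The stated level is therefore exceeded even for one comparison.

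**Working it through.** **Inputs.** Interim boundary 0.003, final level 0.05 two-sided, one look at half the subjects (Statistical analyses; Sample size calculation). Planned size: "we estimate that a total of 90 participants, 30 in each group, would be needed". Recruitment is raised to 100 to allow for 10% dropout, and this inflation reproduces: 90 / (1 − 0.10) = 100. The 30 per group cannot be reproduced, because no effect size, SD or power is given. Half of 90 to 100 is 45 to 50 patients, or about 15 to 17 per arm.

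**Overall level for one comparison.** Under the null, the interim and final statistics are bivariate normal with correlation √0.5. The critical values are 2.968 for 0.003 and 1.960 for 0.05.

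P(|Z1| > 2.968 or |Z2| > 1.960) = 0.0510

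Simulated t tests (400,000 trials, 15 then 30 per arm) give 0.0511. The crude upper bound is 0.003 + 0.05 = 0.053. Solving for the final level that brings the total back to 0.05:

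| Information fraction at the look | Overall level, final test at 0.05 | Final level that restores 0.05 |
|---|---|---|
| 0.4 | 0.0514 | 0.0486 |
| 0.5 | 0.0510 | 0.0490 |
| 0.6 | 0.0506 | 0.0494 |

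Simulation with the final test at 0.049 gives 0.0501.

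**What the interim look adds when several pairs may count.** The same simulation, with the trial declared positive if any listed pair crosses:

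| Pairs that may count | With the 0.003 look | Without any look |
|---|---|---|
| One | 0.051 | 0.050 |
| SR v FR and SR v OR | 0.092 | 0.090 |
| All three | 0.125 | 0.122 |

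The look adds 0.1 to 0.3 percentage points. The rest is multiplicity in the final analysis, a separate matter.

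**How often a stop would rest on one SR comparison.** The article gives no SD, so this takes an assumed range of standardised advantages of SR over both other arms, with 15 per arm and 100,000 simulated trials:

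| Assumed advantage | At least one SR comparison below 0.003 | Share of those stops with only one crossing |
|---|---|---|
| 0.5 SD | 8% | 87% |
| 1.0 SD | 48% | 62% |
| 1.5 SD | 91% | 25% |

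**Precision on failure at a stop.** The only HFNC weaning failure rate in the article is 14 of 133 (10.5%), from the pediatric study in the Background. It is used here as an assumption for both arms. Half-width = 1.96 × √(2 × p × (1 − p) / n).

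- n = 15: 1.96 × √(2 × 0.105 × 0.895 / 15) = 0.219
- n = 17: 1.96 × √(2 × 0.105 × 0.895 / 17) = 0.206
- n = 30: 1.96 × √(2 × 0.105 × 0.895 / 30) = 0.155

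If the rate were 5%, the half-widths at 15, 17 and 30 per arm would be 0.156, 0.147 and 0.110. At 20% they would be 0.286, 0.269 and 0.202. At 10.5%, 17 patients yield 17 × 0.105 = 1.8 expected failures per arm, so the normal approximation is rough and these figures show order of size only.

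**The case against.** The best defence has four parts.

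- **The alpha excess is trivial.** It is 0.1 percentage point, in a trial whose size was not derived from power. This stands, and the excess would not carry the point alone. The 0.003 boundary also resembles an O'Brien-Fleming-type spending of 0.05 at half information, which would pair with a final level near 0.049, so that level may sit in a fuller document. That is possible, but the article sets 0.05 for all tests and states no exception.
- **The P value is not wholly unnamed.** The rule speaks of one outcome and the article has one primary outcome, so time to successful weaning is the natural reading. This stands for the outcome. It does not settle the pair or the analysis set.
- **The error rate of 9% to 12% is not the interim's doing.** A reader might infer that the stopping rule pushes the type I error to about 12%. The figures do not support that: without any look the error is already 9.0% for the two SR comparisons and 12.2% for three pairs. If SR had to beat both arms, these any-pair error rates would not apply.
- **Failure is imprecise anyway.** A reader might infer that early stopping is what leaves the failure rate unresolved. It is not, since the half-width is still about 16 points at full size. Failure may also enter through the definition of successful weaning, but the article does not say how failures are handled in the time analysis.

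**Conclusion.** The point holds at modest size. The part that matters is the trigger: as written, a P value from one of several pairs and either analysis set can end the trial at about 15 to 17 per arm, with the other SR comparison and the failure half of the hypothesis unsettled. Under assumed SR advantages of 0.5 to 1.5 SD, between a quarter and seven-eighths of stops triggered by an SR comparison would rest on only one of the two. On failure, stopping early widens the interval from about 16 to about 21 or 22 points, if the pediatric 10.5% carries over to adults.

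The unadjusted final level is a true but minor error: 0.0510 against 0.05 for one comparison with the look at half information. Multiplicity across pairs should not be charged to the interim look.

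**What to change.** Amend Statistical analyses in three places:

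1. Test the final primary analysis at two-sided 0.049. If the look is not taken at half the information, recompute the level (0.0486 at 0.4, 0.0494 at 0.6).
2. Apply the 0.003 rule only to the ITT analysis of time to successful weaning, and stop for efficacy only if SR is better than both FR and OR at that level.
3. State that failure rates by arm, with confidence intervals, are reviewed before any efficacy stop.

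Requiring SR to win on both comparisons is a design choice. It matches the hypothesis and leaves no choice of trigger after the data are seen. The cost is two or three sentences, a negligible loss of power from 0.05 to 0.049, and a lower chance of stopping early. With 15 per arm and an assumed advantage of 1.0 SD over both arms, 48% of trials have at least one SR comparison below 0.003 and about 18% have both (48% × (1 − 0.62) = 18%).

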### Definitions

Weaning success is defined as a condition in which the patient meets all of the weaning criteria after 24 h of conversion to conventional oxygen therapy. A weaning failure is defined as the patients requiring re-application of the HFNC within 24 h of conversion to conventional oxygen therapy or needing NIV or endotracheal intubation during the HFNC weaning period or within 24 h of conversion to conventional oxygen therapy. If clinical improvement is not seen during follow up, NIV or intubation should be considered according to the clinician’s judgment. Immediate endotracheal intubation will be considered when there are two or more of the following conditions according to standard clinical practice: respiratory rate > 40 breaths/min, arterial pH < 7.2, PaO_2_ < 50 mmHg, signs of high work of breathing such as use of accessory muscle, abdominal paradox, need to secure the airway due to increased sputum, or altered mental status.

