### Outcome measures

The primary outcome is time to successful weaning from HFNC after 24 h of conversion to conventional oxygen therapy. The secondary outcomes will include the success or failure to wean off HFNC (within and after 24 h of conventional oxygen therapy), changes of arterial blood gas analyses (PaO_2_, PaCO_2_, and pH), intolerance rate, length of hospital stay, and in-hospital mortality.

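### The primary outcome is a time to success, but the only test named for it is Student's t test, which cannot represent a randomised patient who fails weaning

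*Protocol article*

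**What the plan says.** Outcome measures: "The primary outcome is time to successful weaning from HFNC after 24 h of conversion to conventional oxygen therapy".

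The Definitions section says of success: "Weaning success is defined as a condition in which the patient meets all of the weaning criteria after 24 h of conversion to conventional oxygen". On the other side, "A weaning failure is defined as the patients requiring re-application of the HFNC within 24 h of conversion to conventional oxygen therapy"; NIV or intubation, during weaning or in those 24 h, also counts as failure.

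Statistical analyses: a Student's t "test will be used to compare continuous variables", with chi-square or Fisher's exact test for categorical ones. No other method is named for the primary outcome. Two analysis sets are given: "For the ITT analysis, all participants enrolled and randomized to one of the three groups will be included", and "For the PP analysis, all participants who complete the study will be included to evaluate the primary and secondary outcomes".

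The Hypothesis section has two parts: simultaneous reduction (SR) weans faster, and it does so with no more failures. Failure to wean is listed separately as a secondary outcome.

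**The concern.** A t test needs one number per patient. An intubated patient has no time to success to supply, and the article assigns none. The test therefore runs on whoever succeeded, and success is a post-randomisation result that the strategies may themselves change. The Discussion section recognises this kind of trade-off when it weighs the speed of immediate withdrawal against its risk of failure.

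Two things are at stake. First, the groups compared are no longer the groups randomised. If patients who wean slowly are also those who fail, an arm with more failures loses its slowest patients and its mean falls. Second, whatever that link may be, the primary test gives no weight to extra failures, although the hypothesis makes them half of the question.

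**Working it through.** **1. The protocol's own figures.** Sample size: 90/(1 − 0.10) = 100, as stated, or about 33 per arm. Failure in the cited paediatric HFNC study: 14/133 = 10.5%, as stated. The cited NIV study reports 74% and 56% success, so 26% and 44% were not successfully weaned.

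**2. The passages side by side.** Outcome: a time that ends in success. Test: a comparison of means. ITT: everyone randomised. All three can hold only if every failing patient receives a time, and the article gives no rule for one.

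**3. Size of the distortion.** Two arms, 33 each, with identical underlying weaning time T = 5·exp(0.5z) h, where z is standard normal. A patient fails when a second standard normal variable, with correlation ρ to z, exceeds c = Φ⁻¹(1 − f), where f is the failure rate. The median of 5 h, the log-SD of 0.5, ρ and the 25% failure rate are assumptions; 10.5% is borrowed from the paediatric study. The mean among successes is

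E[T | success] = 5·exp(0.125)·Φ(c − 0.5ρ)/(1 − f), with 5·exp(0.125) = 5.67 h.

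Example at ρ = 0.7:
- f = 0.25: c = 0.674, Φ(0.324) = 0.627, mean = 5.67 × 0.627/0.75 = 4.74 h.
- f = 0.105: c = 1.254, Φ(0.904) = 0.817, mean = 5.67 × 0.817/0.895 = 5.17 h.
- Difference: −0.43 h, with no true difference.

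The last column comes from 20,000 simulated trials per row: t test on successes, two-sided p < 0.05 in favour of the more-failing arm (nominal 2.5%).

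| ρ | Mean, 25% failing | Mean, 10.5% failing | Difference | Falsely faster |
|---|---|---|---|---|
| 0 | 5.67 | 5.67 | 0 | 2.3% |
| 0.3 | 5.29 | 5.48 | −0.19 | 4.1% |
| 0.5 | 5.02 | 5.33 | −0.31 | 6.1% |
| 0.7 | 4.74 | 5.17 | −0.43 | 8.8% |
| −0.3 | 6.01 | 5.82 | +0.18 | 1.4% |

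Smaller independent runs of 4,000 trials gave 4.3 to 4.6% at ρ = 0.3, 5.6 to 6.4% at 0.5 and 8 to 9.4% at 0.7.

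**4. Sensitivity to the failure rates, at ρ = 0.7.**
- 10.5% in both arms: no bias, 2.5%.
- 15% versus 10.5%: −0.15 h, 4.0%.
- 30% versus 10.5%: −0.56 h, 12.6%.

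**5. What keeping failures does.** A second model used 30 per arm, mean 6 h, coefficient of variation 0.5, and 26% versus 10.5% failure. At ρ = 0.7, the t test on successes declares the more-failing arm faster in 9.0% of trials; a rank test with failures placed last does so in 0.7%. At ρ = 0 the t test is unbiased but rejects in only 4.7% of trials in either direction, so it does not register the extra failures. The rank test rejects in 17%, almost always against the more-failing arm.

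**The case against.** The strongest reply is that nowhere does the article say failures are excluded. ITT is stated to cover everyone, and a rule for failing patients may sit in the full protocol or SAP. It is true that exclusion is an inference. But the test is a stated choice, and it does not suit the stated outcome; the concern does not rest on a missing detail.

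Other objections stand and limit the point:

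- **Failing patients never have a time.** A reader might infer this, but someone put back on HFNC may wean later. The article does not say whether that later time counts.
- **PP selects on success.** A reader might infer this too. Completing the study is not the same as succeeding, because a patient followed to failure may well have completed it.
- **About 10 of 100 patients will lack a value.** The 10.5% is a paediatric rate after up to four attempts, and the protocol cites that study for dropout. The match with the 10% allowance is suggestive, but it does not show that failures are planned as dropouts.
- **SR will look faster.** The direction needs failure to be linked to slow weaning. The protocol holds a patient at each step until criteria are met, so the link is plausible but not established, and a negative link reverses the bias.
- **Identical times are artificial.** SR runs in parallel the steps that the other arms run in sequence, so a real difference is expected. The null model serves only to isolate the bias.
- **Failure is tested separately.** An arm that weans faster but fails more would probably be noticed. That limits the harm; the primary p value would still be conditional on success.

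**Conclusion.** The point holds: the named test does not fit the primary outcome and cannot deliver the ITT comparison the article promises. This follows from the text and needs no simulation.

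The size is conditional. For 25% versus 10.5% failure the spurious advantage runs from 0 to about 0.4 h, and the false-faster rate from nominal to about 9%, as the correlation goes from 0 to 0.7. It stays close to nominal when failure rates are similar. Figures of 9 to 13% belong to the upper part of that range and should not be read as the expected error rate. The documents do not support a prediction that the trial will favour SR wrongly. They do support the conclusion that the primary test, followed literally, would not protect against it.

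**What to change.** For the primary outcome, replace the t test with an analysis of time from randomisation to the conversion that then holds for 24 h, in all randomised patients, over a fixed horizon set in advance. Name ITT as primary and PP as supportive.

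Choose one method beforehand:
- cumulative incidence of success, with weaning failure and death as competing events; or
- a rank test with failures placed last.

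These are not interchangeable, since they weight times and failures differently.

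State whether a success after HFNC re-application counts or the first attempt is decisive. If later successes count, re-application cannot also be treated as a terminal competing event.

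The cost is a few lines of wording and no new data. The drawback is that the effect is reported as a cumulative-incidence, median or rank comparison instead of a difference in mean hours.
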